## Abstract

Supplemental Digital Content is available in the text

## Introduction

1

### Background and rationale

1.1

Hemorrhoidal disease (HD), in its different manifestations, is not only the most frequented grounds of referring for medical attention, but also one of the reasons for the modest deterioration in the quality of life (QOL) that can possibly result in temporary or permanent reduction of work capacities. Today, the Doppler-guided dearterialization of hemorrhoidal arteries and the following suture-fixation mucopexy in the anal canal (synonyms: mucopexy, hemorrhoids lifting, hemorrhoidal artery ligation–suture fixation of hemorrhoidal nodes [HAL-RAR]) is one of the most popular and actively studied methods of the stage II-III HD surgical treatment. A number of publications raise an issue whether it is really necessary to use a Doppler while the localization of the hemorrhoidal arteries is typical in the vast majority of the observations and can be easily determined by palpation.^1^,^2^,^3^,^4^

### Objectives

1.2

#### Research hypothesis

1.2.1

The digital detection of hemorrhoidal arteries pulsation followed by suture ligation and mucopexy may be at least as effective in the treatment of grade II-III hemorrhoids as the Doppler-guided dearterialization of hemorrhoidal arteries.

#### Study objectives

1.2.2

##### Primary objective

1.2.2.1

To determine if the palpation-guided hemorrhoidal arteries ligation and mucopexy is noninferior to Doppler-guided ligation of hemorrhoidal arteries and mucopexy in patients with II-III grade HD at the endpoint of recurrence rate determined by physical examination and patients complaints.

##### Secondary objectives

1.2.2.2

Key secondary objectives:

1.Overall complication rate.2.Patient-reported pain level using visual scale in 1 and 2 months after surgery.3.Patients’ satisfaction rate using a 10-points scale in 6 month and 1 year after surgery.

### Trial design

1.3

HAND study is a prospective, randomized, controlled, unicenter, noninferiority, parallel group, 2-arm trial with 1:1 allocation ratio. Randomization will be performed using block method before the procedure.

## Methods

2

### Study setting

2.1

The study will be conducted at the Clinic of Colorectal and Minimally Invasive Surgery of the Sechenov University Hospital N. 2 in Moscow, Russia. Patients aged form 18 to 75 years of all genders with symptomatic hemorrhoids grade II and III according to Goligher classification will be enrolled in this clinical trial. Thus, in this case, a single-center design can assure sufficient patient recruitment.

### Eligibility criteria

2.2

To be eligible for randomization, an individual must comply with all of the following criteria:

Inclusion criteria:

Symptomatic grade II and III hemorrhoids according to Goligher classification.No other source of anal bleeding than hemorrhoids due to total colonoscopy.Written voluntary informed consent.

Exclusion criteria:

Any previous hemorrhoid surgery (including mini invasive procedures).Anal fistula.Chronic anal fissure with severe spasm of anal sphincters.Any stage colorectal cancer.Oral anticoagulants for congenital disorders of the coagulation system.Pregnancy.

### Interventions

2.3

#### Preoperative preparation

2.3.1

No special preparation is required before procedure.

#### Day of surgery

2.3.2

Under a spinal anesthesia the patient is placed in a modified lithotomy position on the back, with legs spread apart on supports. The operative field is treated with an antiseptic solution twice and draped.

##### Surgical technique

2.3.2.1

Doppler-guided HAL will be performed as following: a lubricating gel is applied to the tip of the transanal hemorrhoidal dearterialization device and, with the patient in the lithotomy position, the proctoscope is introduced into the anal canal. The terminal branches of the superior rectal artery are detected by the Doppler signal 2 to 3 cm above the dentate line. The tip of the instrument is gently tilted and the arteries are ligated with a Z-shaped stitch using 2:0 braided polyglycolic acid suture inserted using a special needle holder through an aperture in the operating proctoscope. Mucopexy: after the hemorrhoid artery ligation, the suture is continued with 3 to 5 sutures applied 5 mm apart, making sure that the last is at least 5 mm above the dentate line. The suture is then tied to create a hemorrhoidopexy. The procedure is repeated after all detected artery ligations.

Finger-guided ligation of hemorrhoidal arteries without Doppler guidance will be performed as following: the exact placement of all terminal branches of the superior rectal artery are found by intraoperative palpation at anal clock 2 to 3 cm above the anorectal junction. Then arteries are ligated with Z-shaped suture using 2:0 braided polyglycolic sutures. Mucopexy is then performed in the same technique as in comparative group

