## Discussion

3

The results of this RCT may demonstrate the absence of significant advantages in Doppler guidance technology for hemorrhoidal arteries detection in HAL-RAR procedures compared with the simple and accessible to any surgeon finger-guided hemorrhoidal arteries detection concerning the efficiency in eliminating hemorrhoidal prolapse and/or hemorrhoidal bleeding. We will analyze frequency of postoperative complications, the intensity of the pain syndrome, the relapse rate, and individual QOL level. It will allow us to conclude whether the HAL-RAR with finger hemorrhoidal artery detection is effective and safety procedure for hemorrhoids disease treatment.

The design of this study has certain limitations. Firstly, there is quite often mismatching of doctors regarding the stage of the HD as well as stage of each hemorrhoidal pile. So the group might be heterogenic regarding the preoperative stage of the HD.

Another issue is the uncertainty of the definition of HD recurrence after surgery. In this protocol, we determined it as appearance of any new symptoms of HD or persistence of previous ones. But we suppose that nevertheless procedure might be effective for preoperatively existed symptoms new ones might appear. So we will try to figure out the difference of preexisting symptoms resolution and appearance of new ones.

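### The two arms set the ligation level from different, undefined landmarks; if these are distinct levels, ligature height varies with arm and the result cannot be attributed to Doppler detection alone

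*Protocol article*

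**What the plan says.** Section 2.3.2.1 (Surgical technique) of the protocol article describes both operations.

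- **Doppler arm:** the terminal branches of the superior rectal artery are "detected by the Doppler signal 2 to 3 cm above the dentate line" and ligated with a Z-shaped stitch.
- **Palpation arm:** the same branches are "found by intraoperative palpation at anal clock 2 to 3 cm above the anorectal junction" and then ligated with the same kind of stitch and suture.
- **Mucopexy:** in the Doppler arm "the suture is continued with 3 to 5 sutures applied 5 mm apart, making sure that the last is at least 5 mm above the"; here the landmark is the dentate line. For the palpation arm, "Mucopexy is then performed in the same technique as in comparative group".

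The primary objective (section 1.2.2.1) is to learn whether "palpation-guided hemorrhoidal arteries ligation and mucopexy is noninferior to Doppler-guided ligation of hemorrhoidal arteries and mucopexy" on recurrence. The Discussion (section 3) says that the results "may demonstrate the absence of significant advantages in Doppler guidance technology for hemorrhoidal arteries detection".

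No section defines the dentate line or the anorectal junction, gives the distance between them, treats them as one level, or says that ligature height is meant to differ between arms.

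**The concern.** The trial asks whether Doppler is needed to find the arteries. To read the result that way, the method of finding them should be the only planned difference between the arms. The technique section otherwise aims at this, with matching target vessels, stitch, suture and mucopexy. The ligation level is the exception, because the same distance is counted from two differently named landmarks.

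If the landmarks are distinct, a surgeon who follows the text literally ligates at different heights in the two arms. Randomization balances patients but does not remove a difference written into the interventions. An effect of height on recurrence could then offset an effect of detection and hide it, or produce a difference that has nothing to do with detection. What is at stake is the attribution to Doppler guidance that the Discussion intends.

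This is not a matter of detail left out of a condensed article. The level is stated for both arms, and the two statements do not match.

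**Working it through.** The plan gives no figure for this point, so there is none to reproduce. The check puts both ligation bands on one scale, in mm above the dentate line.

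**Inputs**

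- Doppler band, section 2.3.2.1: 20 to 30 mm from the dentate line.
- Palpation band, section 2.3.2.1: 20 to 30 mm from the anorectal junction.
- Offset h, the height of the anorectal junction above the dentate line: not in the document. Assumed range 0 to 20 mm.

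**Ligation bands**

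Palpation band = (20 + h) to (30 + h). Overlap with the Doppler band = 30 − (20 + h) = 10 − h mm, or zero once h reaches 10.

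| Assumed h (mm) | Doppler band | Palpation band | Overlap |
|---|---|---|---|
| 0 | 20–30 | 20–30 | 10 mm: identical |
| 5 | 20–30 | 25–35 | 5 mm: half |
| 10 | 20–30 | 30–40 | 0: bands only touch at 30 |
| 20 | 20–30 | 40–50 | none: gap of 40 − 30 = 10 mm |

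So whether the arms differ in height, and by how much, turns entirely on a distance that the document does not give.

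**Does the mucopexy differ as well?**

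The run is 3 to 5 sutures at 5 mm spacing, so 15 to 25 mm long, and must end at least 5 mm above the dentate line.

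- Doppler arm: 20 − 15 = 5 mm; 30 − 25 = 5 mm; 30 − 15 = 15 mm. Permitted end points run from 5 to 15 mm.
- Palpation arm, h = 10: lowest 30 − 25 = 5 mm, highest 40 − 15 = 25 mm.
- Palpation arm, h = 20: lowest 40 − 25 = 15 mm, highest 50 − 15 = 35 mm.

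The permitted end points overlap at h = 10 and still meet, at 15 mm, at h = 20. At h = 0 they are the same. The text therefore does not force a different mucopexy end point at any assumed offset.

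**Effect on recurrence**

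The document says nothing on how recurrence depends on ligature height, so no bias can be calculated or set against the 5% noninferiority margin of section 2.5.

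**The case against.** The strongest reply is that this is loose wording. Both arms share the distance, vessels, stitch, suture and mucopexy, and nothing says that height should differ. The article is loosely worded elsewhere: section 2.7.2 mentions a stapler, although the technique section describes none. If the two terms were meant as synonyms, h is zero and the arms are identical. This stands as a real possibility, and it is why the point is conditional. It does not remove the need for a correction, since a surgeon or reader cannot tell from the text which meaning was intended.

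A second reply is that the primary objective compares two procedures. If the palpation procedure as performed is noninferior, an operation without Doppler does as well on recurrence, whatever the ligature height. This also stands. One may add that arteries are ligated where they are detected, so level is arguably part of the detection method. That has less force, because the text fixes a level for each arm in advance.

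A reader might infer that the trial does compare ligature heights and that neither result could say whether Doppler is needed. The documents do not support this: no offset is given, and noninferiority of the procedures remains testable. A reader might also infer that the mucopexy must differ, or that the palpation arm would need extra sutures. The range of 3 to 5 sutures and the minimum end distance leave room for common end points at every assumed offset, and adding sutures could exceed the stated number.

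**Conclusion.** The point holds in a conditional form and is minor. Section 2.3.2.1 counts the same distance from two undefined landmarks. If these are distinct, ligature height varies with arm: the bands half overlap at an assumed offset of 5 mm, only touch at 10 mm and are separate beyond that. Neither a difference in recurrence nor its absence could then be credited to Doppler detection alone, as the Discussion intends. The test of noninferiority between the procedures as performed is unaffected.

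This rests on the assumed offset of 0 to 20 mm, with the anorectal junction taken as the higher landmark. At zero offset there is no confounding. The size of any bias in recurrence cannot be derived from the document. Which landmark is appropriate is for the investigators, not for this review.

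**What to change.** Reconcile the two descriptions in section 2.3.2.1. Either measure the ligation level in both arms from one common landmark, chosen by the investigators, or state that the two terms mean the same level. Detection method is then the only planned difference between the arms.

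As an option, record ligature height in the operation note, which section 2.7.2 already sends to the electronic case report form, so that the match between arms can be confirmed.

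The cost is one wording amendment and, if the option is taken, one more field in the operation note. No extra patients or procedures are needed.

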#### Early postoperative period

2.3.3

It is defined as the time period from the completion of the surgery and up to 30 days after the surgery. An obligatory regimen of analgesia will be prescribed for each patient, which includes nonsteroidal analgesics, paracetamol, and topical symptomatic drugs. No diet before or after the surgery. The patient will be discharged form hospital after the first defecation if no further medical care is needed.

#### Late postoperative period

2.3.4

It is defined as the period starting at 31st day post surgery. The patient is asked to fill out the questionnaire forms to assess the changes in the QOL and pain level after surgery. To ensure patient compliance to protocol requirements, all subjects will be notified telephonically and/or via e-mail. If the patient is unavailable, they must be contacted at least 3 times within the follow-up timeframe, before considered dropped-out from the study.

### Outcomes

2.4

#### Primary outcome measure

2.4.1

The recurrence of HD is determined as presence any of initial symptoms or appearance of any new symptom of HD: anal bleeding during defecation, prolapse of hemorrhoidal piles, chronic pain, or their combinations.

#### Secondary outcome measures

2.4.2

1.The pain score after surgery will be measured by patient-reported pain level using visual scale ranging from 1 to 10 where 1 is “no pain" and 10 is the worst pain imaginable in 1 and 2 months after surgery.2.QOL assessment (patients satisfaction level): Patients will be asked to rate their own satisfaction of the procedure on a scale from 1 to 10 (with 10 being the best) and were asked whether the procedure helped their symptoms in 6 month and 1 year after surgery.3.Early postoperative complications rate (time frame: 30 days): The rate of complications in 30 days after surgery.

### Sample size

2.5

Considering that this is a noninferiority study, the sample size was calculated using 1-sided Blackwelder test.^[5]^ According to published data, the incidence of recurrence rate of suture ligation of the hemorrhoidal arteries with mucopexy varies from 20% to 30%.^1^,^2^,^3^,^4^ The expected incidence of recurrence rate of HD after digital detection of hemorrhoidal arteries pulsation followed by suture ligation and mucopexy is not more than 35%. The purpose of this study is to show that the outcomes of HAL-RAR procedure with digital detection of hemorrhoidal arteries is noninferior compared to HAL-RAR procedure with Doppler-guided hemorrhoidal arteries detection.

Considering that a = 0.05; the statistical power of the study is 80%; the patients are randomized into 2 groups with 1:1 allocation ratio; the noninferiority margin D = 5%, the required sample size is 204 patients (102 patients in each of the 2 groups).

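### The expected finger-guided recurrence of up to 35% reaches or passes the 5-point margin over the cited 20–30%, so it cannot support the stated 80% power

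*Protocol article*

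**What the plan says.** All the relevant figures are in the Sample size section (2.5) of the protocol article.

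- **Method:** "the sample size was calculated using 1-sided Blackwelder test".
- **Cited rate:** "the incidence of recurrence rate of suture ligation of the hemorrhoidal arteries with mucopexy varies from 20% to 30" percent. The section does not say whether this refers to Doppler-guided ligation, finger-guided ligation or both.
- **Expected rate in the experimental arm:** the expected recurrence after "digital detection of hemorrhoidal arteries pulsation followed by suture ligation and mucopexy is not more than 35" percent.
- **Error rates:** "Considering that a = 0.05; the statistical power of the study is 80" percent.
- **Margin:** "the noninferiority margin D = 5" percent, read here as 5 percentage points on the difference in recurrence.
- **Result:** "the required sample size is 204 patients (102 patients in each of the 2 groups").

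No single expected rate is given for either arm. The Research hypothesis section (1.2.1) supposes that finger guidance is no less effective than Doppler guidance. The Primary objective section (1.2.2.1) makes the comparison one of noninferiority to Doppler-guided ligation.

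**The concern.** A noninferiority sample size rests on an assumed true difference that lies inside the margin. Power is the chance of excluding the margin when that assumption is true. Here the only figure attached to the experimental arm is an upper bound, and that bound is 5 points above the top of the cited range and 15 points above the bottom. Part of what the plan calls expected is therefore a state in which noninferiority is false.

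The stated power and sample size are at stake. A reader cannot tell which pair of rates the 80% refers to. If the 35% is taken at face value as the planning value, 80% power cannot be reached.

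**Working it through.** **Inputs.** Doppler rate pC = 20%, 25% (the midpoint) or 30%, from the cited range and taken as the reference by assumption. Finger-guided rate pT = 35%, the stated ceiling. Margin D = 0.05. One-sided alpha 0.05 (z = 1.6449). Power 80% (z = 0.8416). 102 patients per arm.

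**Formulas** (recurrence is an adverse outcome; unpooled variance).

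- n per arm = [pC(1−pC) + pT(1−pT)] × (1.6449 + 0.8416)² / (D − (pT − pC))², where (2.4865)² = 6.1827. It applies only when D − (pT − pC) is positive.
- Chance of showing noninferiority = Φ((D − (pT − pC))/SE − 1.645), with SE = √([pC(1−pC) + pT(1−pT)]/102).

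**Step 1: the plan's own figure.** At pT = 35% the distance to the margin, D − (pT − pC), is 0, −0.05 or −0.10 for pC = 30%, 25% or 20%. No n exists, so 102 per arm cannot be reproduced from the stated expectation. Equal rates do not give it either (step 3). Among pairs drawn from 20, 25, 30 and 35%, at one-sided 0.05 and 80% power, 102 appears only for Doppler 30% and finger guidance 20%: (0.21 + 0.16) × 6.1827 / 0.15² = 101.7, rounded up to 102. That is a 10-point advantage of finger guidance, which the section does not state. The pair was found by search, so it does not show how the sponsor arrived at 204.

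**Step 2: true finger-guided rate at the 35% ceiling, 102 per arm.**

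| Doppler rate | Excess (points) | SE | z | Chance of showing noninferiority |
|---|---|---|---|---|
| 30% | 5 | 0.0655 | 0/0.0655 − 1.645 = −1.645 | 5.0% |
| 25% | 10 | 0.0638 | −0.05/0.0638 − 1.645 = −2.43 | 0.8% |
| 20% | 15 | 0.0616 | −0.10/0.0616 − 1.645 = −3.27 | 0.05% |

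The 5.0% in the first row is simply alpha, because the true difference lies on the margin; it stays at 5% whatever the sample size. In the other two rows the chance falls towards zero as n grows. At one-sided 0.025 the three figures are 2.5%, 0.3% and 0.02%.

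**Step 3: expected rates inside the margin, illustrated by equal rates.**

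| Rate in both arms | SE at 102 per arm | Power at 102 per arm | n per arm for 80% |
|---|---|---|---|
| 20% | 0.0560 | 22.6% | 0.32 × 6.1827/0.0025 → 792 |
| 25% | 0.0606 | 20.6% | 0.375 × 6.1827/0.0025 → 928 |
| 30% | 0.0642 | 19.3% | 0.42 × 6.1827/0.0025 → 1039 |

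In total that is 1584 to 2078 patients for 80% power, against the 204 planned.

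**Step 4: if 20–30% is not the Doppler rate.** The ceiling of 35% falls inside the margin only if the Doppler rate is above 30%. With 35% in both arms, for example, 102 per arm gives 18.5% power, so the stated 80% is not recovered that way.

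**The case against.** The strongest case on the other side has four parts.

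- **The 35% is a ceiling.** Rates of 25% in both arms satisfy the cited range, the ceiling and the margin together, and the research hypothesis assumes no disadvantage. This stands. A reader might infer that the three statements cannot all be true, or that the plan predicts inferiority; the text supports neither. What remains is that a ceiling is not a planning value, and no other rate is given for this arm.
- **30% plus 5 points is 35%.** The ceiling may simply be the margin applied to the top of the cited range. This is possible. In that case it is a limit described as an expected rate, and it agrees with the margin only at a Doppler rate of exactly 30%; at 20% or 25% the margin gives 25% or 30%.
- **There is only one acceptance limit.** A reader might infer that the section carries two competing limits, or that a finger-guided rate below 35% would count as success by itself. The documents do not support this. Only D is called the margin, the objective and the Sample size section both make the comparison with Doppler guidance, and no single-arm criterion appears anywhere. A 35% finger-guided rate against 20% with Doppler would fail noninferiority under the plan as written.
- **The 20–30% is not labelled as Doppler.** This stands. The Background section cites the same references for publications that question the need for Doppler, and those sources are not at hand. The reference rate is therefore an assumption.

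**Conclusion.** The point holds as a fault in a sample-size input. The only rate given for the finger-guided arm extends to or past the margin for every reference rate in the cited range. At that end of the expectation the chance of showing noninferiority is at most 5%, and no sample size gives the stated 80%.

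It cannot be separated from the power calculation. Once the 35% is replaced by equal rates within the cited range, 102 per arm gives about 19–23% power, so correcting the sentence without restating the power would leave the section inconsistent.

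The conclusion assumes that 20–30% is the Doppler rate, that D is an absolute difference, and that alpha 0.05 is one-sided, as the named test implies. A one-sided 0.025 makes every figure less favourable: 14%, 13% and 12% for equal rates of 20%, 25% and 30%.

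**What to change.** In section 2.5, replace the sentence containing the 35% with one named expected rate for each arm, with a difference inside the margin, and say which technique the cited 20–30% describes. Then restate the power of 204 patients under those rates. For equal rates, the text could read:

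> Recurrence is expected to be X% in both arms. With 102 patients per arm, a one-sided alpha of 0.05 and a margin of 5 percentage points, the power is about Y%.

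Here Y is 23, 21 or 19 for X = 20, 25 or 30. If the sponsor meant 35% as 30% plus the margin, it should be described as the limit that follows from a 30% reference, not as an expected rate. If the sponsor in fact assumed an advantage of finger guidance, that assumption should be stated and justified.

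**Cost.** A few sentences; no extra patients or data are needed to make the correction. The downside is that the sponsor must commit to one reference rate and report a much lower power. Keeping 80% power under equal rates would be a separate decision about trial size (1584 to 2078 patients).

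### Section 2.5: 102 patients per group do not give 80% power at a 5-point margin; with equal recurrence of 20–30% the power is about 19–23%

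*Protocol article*

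**What the plan says.** All the inputs are in section 2.5 (Sample size) of the protocol article.

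- Test: "the sample size was calculated using 1-sided Blackwelder test".
- Error rates: "Considering that a = 0.05; the statistical power of the study is 80" per cent, with 1:1 allocation.
- Margin and result: "the noninferiority margin D = 5%, the required sample size is 204 patients (102 patients in each of the 2 groups").
- Published recurrence: "the incidence of recurrence rate of suture ligation of the hemorrhoidal arteries with mucopexy varies from 20% to 30" per cent.
- Finger-guided arm: the expected recurrence after "digital detection of hemorrhoidal arteries pulsation followed by suture ligation and mucopexy is not more than 35" per cent.

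The section does not say which two true rates were entered. The research hypothesis (section 1.2.1) claims only that finger guidance is no less effective than Doppler guidance, and the primary objective (section 1.2.2.1) is noninferiority on recurrence. Recurrence is an unfavourable outcome (section 2.4.1), so a higher rate is worse.

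**The concern.** A 5-point margin on an outcome with a 20–30% event rate normally calls for many hundreds of patients per group, so 102 looks far too small. Both routes that the text suggests fail to explain it. Equal rates need a much larger trial. A finger-arm rate of 35% would lie at or beyond the margin, where no sample size gives 80% power.

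The primary objective is at stake. If the two techniques are truly equal, a trial with about 20% power misses noninferiority about four times in five. Readers and ethics reviewers have been told that the chance of missing it is one in five. A failed result could then be misread as evidence in favour of Doppler guidance.

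**Working it through.** **Inputs (section 2.5).** One-sided α = 0.05, so z = 1.645. Power 80%, so z = 0.842. D = 0.05, read as absolute percentage points. n = 102 per group. The section attributes the 20–30% to suture ligation with mucopexy without naming Doppler; treating it as the reference rate is an assumption.

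**Formula** (Blackwelder, unpooled variance; pC is Doppler recurrence, pT is finger-guided recurrence):

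n per group = (1.645 + 0.842)² × [pC(1−pC) + pT(1−pT)] / [D − (pT − pC)]², where (1.645 + 0.842)² = 6.183 (unrounded z values).

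Power = Φ([D − (pT − pC)]/SE − 1.645), where SE = √{[pC(1−pC) + pT(1−pT)]/n}.

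**1. Trying to reproduce 102 with D = 0.05.**

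- pC = 0.30, pT = 0.20: 6.183 × 0.37/0.15² = 101.67, so 102 (power 80.1%).
- pC = 0.25, pT = 0.16: 6.183 × 0.3219/0.14² = 101.54, so 102.

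The required advantage is thus 10 points from a 30% reference and 9 points from 25%. From a 20% reference it is slightly under 8: pT = 0.1225 gives 6.183 × 0.2675/0.1275² = 101.7. In every case finger guidance must be clearly better.

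**2. Equal true rates, the usual noninferiority planning case.**

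| Recurrence in both arms | n per group for 80% | SE at 102 | Power at 102 |
|---|---|---|---|
| 20% | 6.183 × 0.320/0.0025 = 791.4, so 792 | 0.0560 | Φ(0.893 − 1.645) = 22.6% |
| 25% | 6.183 × 0.375/0.0025 = 927.4, so 928 | 0.0606 | Φ(0.825 − 1.645) = 20.6% |
| 30% | 6.183 × 0.420/0.0025 = 1,038.7, so 1,039 | 0.0642 | Φ(0.779 − 1.645) = 19.3% |

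The Farrington–Manning variance gives nearly the same numbers (794, 929 and 1,039). Reading α as one-sided 0.025 widens the gap: 1,005, 1,178 and 1,319 per group.

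**3. If the finger-arm rate really were 35%.** The excess over 30%, 25% and 20% is 5, 10 and 15 points, so D − (pT − pC) is 0, −5 and −10 points. Power at 102 is 5.0%, 0.8% and 0.05%. If both arms were at 35%, 1,126 per group would be needed and power at 102 would be 18.5%.

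**4. Precision of 102 per group at 20–30%.** The one-sided 95% limit lies 1.645 × SE = 9.2 to 10.6 points above the observed difference. The two-sided 95% half-width is 1.96 × SE = 11.0 to 12.6 points. To put the one-sided limit below 5, finger guidance must be observed about 4 to 6 points better (5 − 9.2 = −4.2; 5 − 10.6 = −5.6).

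**5. Margin that 102 supports at 80% power with equal rates.** (1.645 + 0.842) × SE = 13.9, 15.1 and 16.0 points at 20%, 25% and 30%.

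**The case against.** The strongest defence is that section 2.5 never says the rates were assumed equal. A planning pair of 30% for Doppler and 20% for finger guidance, both within the cited range, gives exactly 102 with no arithmetic error. That is correct, and it means the 19–23% depends on the equal-rates assumption. It does not rescue the text: a 10-point advantage is stated nowhere, the hypothesis claims only no loss of effect, and the one figure given for the finger arm lies above the cited range.

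Three stronger readings are tempting, and the document does not support them.

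- *That the cause is known.* Entering recurrence rates as success rates, 20% for control and 30% for finger guidance, also yields 102. So does an undisclosed 30% versus 20% assumption, and a margin of 16 points with 30% in both arms comes to 6.183 × 0.42/0.0256 = 101.4. The entry error is one possibility; the text cannot confirm it.
- *That exactly 10 points is the only advantage that works.* The 16% versus 25% pair shows otherwise.
- *That the trial is planned at 35% versus 30%.* The 35% is an upper bound and may simply be 30% plus the margin written out. On that reading it agrees with D, and 5% power there is just the type I error at the boundary of the null hypothesis.

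Condensation into an article does not explain the mismatch, since the article states a definite power, margin and sample size. A dropout allowance, which section 2.5 does not mention, would only raise the number.

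**Conclusion.** The point holds. No pair of rates that section 2.5 adopts gives 102 per group at a 5-point margin, one-sided 0.05 and 80% power. With equal recurrence of 20–30%, 204 patients provide roughly a quarter of the stated power, and the required size is about 8 to 10 times larger (792/102 = 7.8; 1,039/102 = 10.2).

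This rests on three readings: D is absolute, α is one-sided 0.05, and the cited 20–30% is the reference rate. A one-sided 0.025 would make the gap larger. The origin of the 102 remains open, and so does the meaning of the 35%. The conclusion depends on neither.

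**What to change.** In section 2.5:

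1. Withdraw the statement that 204 patients give 80% power at D = 5 points.
2. State the assumed recurrence in each arm, on the recurrence scale.
3. Restate the power of 204 patients as about 19–23% under equal rates of 20–30%, and note that 80% requires a true advantage for finger guidance of about 9–10 points at reference rates of 25–30% (slightly under 8 at 20%).
4. Give the precision: a one-sided 95% limit about 9–11 points above the observed difference, and a two-sided 95% interval of about ±11–13 points.
5. Say whether 35% is the noninferiority limit (30% + 5%) or an expected rate, and reconcile it with D.

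The cost is a rewritten section and a much less favourable power figure. No extra patients are needed to correct the statement, but the correction does not raise the power. Reaching 80% at 5 points with equal rates would take 1,584 to 2,078 patients in total (2 × 792 to 2 × 1,039).
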